## Abstract

**Background:**

Atrial fibrillation (AF) is common in older people and increases the risk of stroke. The feasibility and effectiveness of the implementation of a patient-led AF screening program for older people are unknown.

**Objective:**

This study aims to examine the feasibility and effectiveness of an AF screening program comprising patient-led monitoring of single-lead electrocardiograms (ECGs) with clinician-coordinated central monitoring to diagnose AF among community-dwelling people aged ≥75 years in Australia.

**Methods:**

This is a nationwide randomized controlled implementation trial conducted via the internet and remotely among 200 community-dwelling adults aged ≥75 years with no known AF. Randomization will be performed in a 1:1 allocation ratio for the intervention versus control. Intervention group participants will be enrolled in the monitoring program at randomization. They will receive a handheld single-lead ECG device and training on the self-recording of ECGs on weekdays and submit their ECGs via their smartphones. The control group participants will receive usual care from their general practitioners for the initial 6 months and then commence the 6-month monitoring program. The ECGs will be reviewed centrally by trained personnel. Participants and their general practitioners will be notified of AF and other clinically significant ECG abnormalities.

**Results:**

This study will establish the feasibility and effectiveness of implementing the intervention in this patient population. The primary clinical outcome is the AF detection rate, and the primary feasibility outcome is the patient satisfaction score. Other outcomes include appropriate use of anticoagulant therapy, participant recruitment rate, program engagement (eg, frequency of ECG transmission), agreement in ECG interpretation between the device automatic algorithm and clinicians, the proportion of participants who complete the trial and number of dropouts, and the impact of frailty on feasibility and outcomes. We will conduct a qualitative evaluation to examine the barriers to and acceptability and enablers of implementation. Ethics approval was obtained from the human research ethics committee at the University of Sydney (project number 2020/680). The results will be disseminated via conventional scientiﬁc forums, including peer-reviewed publications and presentations at national and international conferences.

**Conclusions:**

By incorporating an integrated health care approach involving patient empowerment, centralized clinician-coordinated ECG monitoring, and facilitation of primary care and specialist services, it is possible to diagnose and treat AF early to reduce stroke risk. This study will provide new information on how to implement AF screening using digital health technology practicably and feasibly for older and frail populations residing in the community.

**Trial Registration:**

Australian New Zealand Clinical Trials Registry ACTRN12621000184875; https://www.anzctr.org.au/Trial/Registration/TrialReview.aspx?id=380877

**International Registered Report Identifier (IRRID):**

DERR1-10.2196/34778

## Introduction

### Background

The prevalence and incidence of atrial fibrillation (AF) increase with age and is common among older people [1-4]. A recent study estimated that the global prevalence of AF is 59.7 million [4]. Approximately 70% of individuals with AF are aged between 65 and 85 years [5]. AF has been reported to account for 36% of all ischemic strokes, of which 85% are inadequately anticoagulated [6]. If AF is detected early and managed with appropriate anticoagulation therapy, the stroke risk and subsequent stroke-related disability and mortality can be reduced significantly [7]. Unfortunately, it was estimated that 1% of the general population and 1.4% of people aged ≥65 years were living with undiagnosed AF, as reported in a systematic review that combined data from 30 cross-sectional studies (n=122,571) [8]. Hence, the opportunity for anticoagulation therapy to reduce stroke risk for these patients is missed.

Several guidelines have recommended opportunistic screening for AF [9-12]. However, studies suggest that one-off opportunistic screening approaches have a low yield for identifying AF. For example, a recent cluster randomized trial of opportunistic screening using pulse palpation, electronic blood pressure measurement with an AF algorithm, and a handheld single-lead electrocardiogram (ECG) device versus usual care for detection of AF in primary care patients (involving 9218 patients in the intention-to-screen group, 55% women, mean age 75.2 years vs 9526 patients in the usual care group, 54.3% women, mean age 75.0 years) found that opportunistic screening did not improve AF detection compared with usual care [13]. On the contrary, repeated heart rhythm monitoring over a duration increased the yield of AF detection. Petryszyn et al [14] reported in a systematic review that repeated heart rhythm monitoring with ECG devices over periods ranging from 2 weeks to 12 months had higher AF detection rates compared with one-off opportunistic screening approaches: 2.1% (95% CI 1.5-2.8) with repeated ECG screening versus 1.2% (95% CI 0.8-1.6) with opportunistic screening (*P*<.05). Although many guidelines advocate the use of 12-lead ECG for opportunistic screening, these may limit locations where screening may occur and demand a higher skill level to operate 12-lead ECG devices [15,16]. Mobile single-lead handheld ECG devices are easier to use with better time efficiency compared with 12-lead ECG machines, and these single-lead handheld ECG devices have been used in several AF screening studies [15].

Recent systematic reviews, including 8180 single-lead ECG tracings, show that mobile handheld single-lead ECG devices have high accuracy for diagnosing AF [17]. These devices are available to the public and clinicians. However, a national survey reported that although general practitioners (GPs) are aware of the devices, they rarely conduct AF screening in their busy clinical practice [18]. Clinician-led AF screening faces barriers because clinicians are facing competing clinical priorities and time constraints [19]. Alternative strategies for early detection and management of AF are needed. Patient-led AF screening through self-recording of single-lead ECG using mobile handheld ECG devices could be an alternative. A randomized controlled trial (RCT) involving 7173 community-dwelling older people aged 75 to 76 years in Sweden reported that screening using patient-activated intermittent ECG recordings with a handheld ECG device (Zenicor) twice daily over 2 weeks, when the participants noticed palpitations, increased new AF detection fourfold [20]. Similarly, in an RCT of AF screening using a handheld ECG device (AliveCor Kardia) in 1001 participants aged ≥65 years and with CHADS-VASc (congestive heart failure, hypertension, age ≥75 [double score], diabetes, stroke [double score], vascular disease, age 65 to 74 and sex category) score ≥2, the detection rate of new AF after 12 months was 3.8% in the monitored group versus 0.1% in the control group (hazard ratio 3.9, 95% CI 1.4-10.4; *P*=.007) [21]. Another RCT of AF screening using a 2-week ambulatory ECG patch (Zio XT), one at baseline and another at 3 months in 856 participants aged ≥75 years with hypertension, increased new AF detection rate 10 folds (5.3% in the monitored group vs 0.5% in the control group; relative risk: 11.2; 95% CI, 2.7-47.1; *P*=.001) [22]. These studies [20-22] suggest the potential of patient-led approaches to AF screening but still leave questions on how to implement these approaches and the generalizability of these approaches. Unanswered questions about the implementation of AF screening programs include whether such programs can be implemented alongside existing health care systems; whether regular self-screening with mobile devices is feasible and acceptable in older adults; what is the feasibility, resource use, and clinician acceptability of real-world implementation of such programs; what is the time taken by services overseeing and monitoring such programs in terms of reviewing and interpreting large amounts of ECG data; and what strategies can be applied to optimize the use of resources. In addition, there is less data on the barriers to and enablers of the implementation of such programs, longer self-monitoring periods, and implementation in subgroups (such as older people who are frail and people living in remote areas) in which these strategies may not work. A recent systematic review reported that the prevalence of frailty in patients with AF was up to 75% [23]. More studies are needed to better assess whether such mobile health devices can be used effectively and implemented in programs at a large scale among older people who are frail.

There is also a lack of information about the role and importance of patient empowerment with respect to the implementation of AF screening. The World Health Organization promotes patient empowerment (ie, training patients to perform and engage in health-related behaviors within their familiar setting) as it can potentially lead to positive health outcomes [24]. Patient empowerment can be incorporated in patient-led AF screening by training patients to self-record single-lead ECGs. However, patient empowerment has its limitations; that is, patients face automated ECG interpretation results that are often beyond their competence to understand and act upon, and it is impractical to have every ECG result individually and regularly checked by their clinicians. A centralized monitoring system is a feasible way of remotely monitoring a patient’s heart rhythm [25].

The processes of the screening program can vary in their actual implementation because of diverse contexts and participant characteristics (both patients and clinicians); for example, participants may be incapable of or not engage in performing self-recording of ECG, or they may not follow up with (or do not have access to) their clinician after a clinically significant abnormality is detected and notified. Process variations can affect outcomes. Therefore, it is important to evaluate the processes with the aim of better understanding why variations occur and how to improve the processes to achieve an effective intervention and identify contextually relevant strategies to scale up the screening program to benefit larger populations.

In summary, there are gaps in our knowledge regarding the feasibility, effectiveness, and acceptability of patient-led AF screening by remote patient self-recording with centralized clinician-supported monitoring of single-lead ECGs in older community-dwelling people who are frail. The Mass AF screening program (Figure 1) is designed for implementation among community-dwelling people aged ≥75 years. It comprises the provision of a handheld ECG device and training of participants to self-screen on weekdays and transmit ECGs for review by a central monitoring team. We aim to implement and evaluate this AF self-screening program in which older people in the community are empowered to perform repeated heart rhythm monitoring using a single-lead handheld ECG device and connected with health care providers who review and support the diagnosis of AF and management by primary care and specialist services. We hypothesize that the proposed self-screening model of care may lead to several positive outcomes, including a feasible and scalable model for implementing patient-led AF screening in community-dwelling older people, improved patient satisfaction by empowering them with the relevant knowledge and skills to perform self-screening [24], and thereby higher adherence to the screening program [26,27].

**Figure 1 figure1:**
[figure not shown]
Overview of the *Mass AF* screening program: patient-led self-recording of electrocardiograms (ECGs) with the clinician-coordinated centralized system. AF: atrial fibrillation; GP: general practitioner.

### Objective

Our study objectives are to (1) compare AF ascertainment rates in the intervention and control groups; (2) evaluate the feasibility of the intervention, including assessing participant satisfaction, acceptability, barriers, and enablers and how frailty influences these assessments; and (3) assess agreements between the ECG device automatic algorithm and clinician interpretation.

Alongside these objectives, the specific objectives of the process evaluations are as follows:

To assess the fidelity of the screening program (ie, whether the intervention was delivered as intended), participant engagement with the intervention in terms of the frequency of ECG recordings, and reach (eg, the socioeconomic and frailty profiles of participants and how these profiles affect the engagement and outcomes)To evaluate the feasibility of the screening program from the perspective of participants and clinicians to gain a deeper understanding of barriers and enablers; this includes an examination of the mechanisms of impact; that is, an examination of the potential causal mechanisms through which the intervention results in the adoption of self-screening by understanding how patients and clinicians interact with the screening programTo explore any factors external to the screening program that may have affected implementation (ie, the community-dwelling environment, access to health care services, and GP views and attitudes), including identification of resources and implementation processes required for effective uptake and implementation of the screening program

## Methods

### Study Design

This is a 2-arm, randomized, open-label, waitlist-controlled trial in community-dwelling people aged ≥75 years. We will also conduct a process evaluation of this study. Randomization in the ratio of 1:1 is stratified by participant frailty status (frail or nonfrail; Multimedia Appendix 1). Participant frailty was determined using the FRAIL (Fatigue, Resistance, Ambulation, Illnesses, and Loss of Weight) scale based on five components: *fatigue*, *resistance* (inability to climb stairs), *ambulation* (inability to walk a certain distance), *illness*, and *loss of weight* [28,29]. The intervention group will commence the monitoring program for 12 months upon enrollment. The control group will be waitlisted for the first 6 months and then commence the monitoring program in the subsequent 6 months. The steps involved for enrollment, randomization, intervention, control, and exit from the program are outlined in the study flowchart (Figure 2), and descriptions of the screening program are provided in the following sections.

**Figure 2 figure2:**
[figure not shown]
Flowchart of the *Mass AF* screening program. AF: atrial fibrillation; ECG: electrocardiogram; GP: general practitioner.

### Study Population

Our target population involves older people living independently in the community outside of a hospital, nursing home, or similar institutional residence. The inclusion criteria are as follows: community-dwelling people aged ≥75 years, having a smartphone or electronic device that can operate the AliveCor Kardia mobile app, and being able to understand instructions in English. Individuals with the following conditions will be excluded: previously confirmed diagnosis of AF, having an implantable cardiac monitor, pacemaker or defibrillator, dementia, inability to provide informed consent, and those with a medical illness with an anticipated life expectancy of <3 months.

### Intervention Group: AF Self-screening and Monitoring Program

Participants allocated to the intervention will immediately commence the monitoring program. They will be provided with a small handheld single-lead Kardia ECG device (AliveCor Inc), which has been cleared by the Food and Drug Administration and approved by the Therapeutics Goods Administration. After the participants receive the device, they will receive a phone call from research assistants who will help them to set up the device, including downloading the Kardia app to the mobile phone, setting up reminders to record ECG in the app, and setting up a Kardia user account. The research assistants will create a participant profile in the central monitoring portal, which will generate a unique 12-digit code for the participant. Research assistants will inform participants of their unique 12-digit code via SMS text message or over the phone. The participant will enter the 12-digit code in their Kardia user account, and once this step is completed, the Kardia user account will be connected to the central monitoring portal. Participants can commence recording the ECGs, which will be transmitted to their personal profiles in the central monitoring portal.

Research assistants will take participants through the steps of recording an ECG. Participants will record a single-lead ECG trace by placing 2 fingers of each hand steadily on 2 small touchpads (3 cm × 3 cm) of the device for 30 seconds on weekdays. The ECG device will be connected to the mobile phone wirelessly via the Kardia app that they have downloaded. An ECG trace will appear on the participants’ mobile phones, and participants will be able to record notes in the ECG trace. We will encourage them to note the activities they performed before recording the ECG. The ECG and notes will be automatically transmitted to the central monitoring portal. The training conducted over the telephone or video call between research assistants and participants will take approximately 30 to 60 minutes per participant. In the context of the COVID-19 pandemic, all study-related procedures will be conducted remotely using phone calls or video calls (if participants have access to and prefer this modality). To ensure that participants are confident in using the device, research assistants will call each participant to confirm that they are able to record an ECG. Participants will be encouraged to have a family member who may assist them in the process. After the training, participants will also receive an SMS text message with a weblink to an instructional video created by the device manufacturer. The short training video will serve as a reference for participants to refresh their memory on how to record a single-lead ECG. The research team will contact participants if they have not recorded any ECGs for 3 consecutive days to find out and address the causes, if possible.

Before commencing the study, participants will be advised that in the event of experiencing symptoms (eg, syncope, chest pain, palpitations, and shortness of breath) that are severe in nature or that are of concern to the participants, to present to their local medical physician or hospital for assessment as soon as possible.

### Control Group: Usual Care During Waiting Period

Participants allocated to the control group will have usual care and be told that they have been waitlisted to start the monitoring program in 6 months. During the 6-month waiting period, it is expected that participants in the waitlist group will visit their GPs as per their usual health care needs, and their GPs will provide care and referrals as usual.

### Sample Size

In computing the sample size required to assess the primary feasibility outcome, we will evaluate the proportion of participants reporting being satisfied or very satisfied that their heart rhythm was monitored in the past 6 months in the intervention group versus the control group. We arbitrarily set that 50% of the participants in the control group will be satisfied or very satisfied. With reference to the literature that reported a proportion of 67% [30] to 82% [31] of older people were satisfied or very satisfied with the use of technology-enabled monitoring at home, we postulate that there will be an absolute 30% increase in satisfaction in the intervention group compared with the control group. Our study will have 80% power, using a 5% level of significance, to detect an absolute difference of 30% in satisfaction between the 2 groups. A sample size of 100 participants aged ≥75 years is required to assess the primary feasibility outcome

To calculate the sample size required to evaluate the primary clinical outcome of AF detection rate, we set an AF detection rate of 10% in the intervention group and 1% in the control group, in accordance with a recent study [22]. At 80% power, a 2-sided test, and α .05, we estimate that a sample of 200 participants will be needed to detect a significant difference in AF detection between the intervention and control groups. Therefore, a total of 200 participants will be recruited for this trial to assess the primary clinical outcome.

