### Randomization

Participants will be randomized to the intervention or control group on a 1:1 basis stratified by baseline measure of frailty (ie, frail or not frail according to the FRAIL score) [28,29] and using permuted blocks of sizes 4 and 6. The statistician has generated a randomization list using the RandomiseR package in R software (R Foundation for Statistical Computing) [32]. The randomization list will be input into the REDCap (Research Electronic Data Capture) [33] database, which captures participant demographic and baseline data and survey findings (Multimedia Appendix 1). The statistician and principal investigators will be unaware of patient allocation until after the completion of the study.

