### Anticipated Challenges and Limitations

All study procedures have been designed to be conducted remotely by telephone or video interface to facilitate this study in the context of the COVID-19 pandemic. Therefore, the collection of baseline data and medical history relies on participants’ self-reported information. There is a potential for loss to follow-up in older patients who are frail; for example, participants do not record ECGs. We will attempt to minimize this by following up with patients when no ECG is received for 3 consecutive days. There may be a potential selection bias in this study based on the inclusion criteria. For example, this trial is limited to older people who can understand English and have a smartphone. These participants may come from higher socioeconomic communities and represent a more motivated cohort than the general population of older people.

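### The AF detection rates behind the sample size (10% vs 1%) are attributed to a study that the protocol itself reports as 5.3% vs 0.5%; at those rates 200 participants give about 53–57% power, not 80%.

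*Protocol article*

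**What the plan says.** The Sample Size section of the protocol article states for AF detection: "we set an AF detection rate of 10% in the intervention group and 1% in the control group, in accordance with a recent study [22"]. It continues: "At 80% power, a 2-sided test, and α .05, we estimate that a sample of 200 participants will be needed". It concludes that "a total of 200 participants will be recruited for this trial to assess the primary clinical outcome". The feasibility outcome needs only 100, so AF detection alone sets the trial's size. Allocation is equal ("Participants will be randomized to the intervention or control group on a 1:1 basis"), which gives 100 per arm.

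The Background describes reference 22 as a trial of a 2-week ECG patch, applied "one at baseline and another at 3 months in 856 participants aged ≥75 years with hypertension, increased new AF detection rate 10 folds". The rates it gives are "5.3% in the monitored group vs 0.5% in the control group", with a relative risk of 11.2.

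The Analysis section compares new AF between groups with the chi-square test at two-tailed P<.05. Textbox 1 places the comparison at 6 months.

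**The concern.** Reference 22 is the only support offered for 10% vs 1%, and the protocol's own account of it gives roughly half of each rate. No other sentence explains the increase, for example by longer monitoring or a higher-risk population. The randomized trials summarised in the Background do not supply 10% either. The highest monitored-group rate quoted there is the 5.3% of reference 22. The handheld-device trial shows 3.8% at 12 months, although it enrolled people from age 65 and is not a close match.

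A reader would take the 80% power as grounded in published rates. If the true effect were the one seen in reference 22, the trial would have a little under an even chance of missing it. A non-significant result could then be mistaken for evidence that patient-led screening does not raise detection.

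**Working it through.** **Inputs.** Assumed rates 10% and 1%, power 80%, two-sided α of .05 and total 200 (Sample Size); 1:1 allocation (Randomization); cited rates 5.3% and 0.5% (Background); chi-square test (Analysis). The article names no sample-size formula, so the pooled-variance normal approximation without continuity correction is tried first.

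**Formulas.** With d = p1 − p2, p̄ = (p1 + p2)/2, A = √[2p̄(1−p̄)] and B = √[p1(1−p1) + p2(1−p2)]:

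- n per arm = (1.960·A + 0.842·B)² / d²
- power = Φ[(d√n − 1.960·A) / B]

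**Step 1: reproduce the plan's figure (10% vs 1%).**

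- d = 0.09, p̄ = 0.055, A = √0.10395 = 0.3224, B = √0.0999 = 0.3161
- n = (0.6319 + 0.2660)² / 0.0081 = 99.5, so 100 per arm and 200 in total
- power at 100 per arm = Φ[(0.900 − 0.6319)/0.3161] = Φ(0.848) = 80.2%

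The stated 200 is reproduced exactly. Other formulas do not give it: 97 per arm unpooled, 80 arcsine, 121 with continuity correction.

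**Step 2: the same formula at the cited rates (5.3% vs 0.5%).**

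- d = 0.048, p̄ = 0.029, A = √0.056318 = 0.2373, B = √0.055166 = 0.2349
- power at 100 per arm = Φ[(0.480 − 0.4651)/0.2349] = Φ(0.063) = 52.5%
- n = (0.4651 + 0.1977)² / 0.002304 = 190.7, so 191 per arm and 382 in total

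**Step 3: does the answer depend on the approximation?** Power at 100 per arm:

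| Method | 10% vs 1% | 5.3% vs 0.5% |
|---|---|---|
| Pooled normal approximation | 80.2% | 52.5% |
| Exact enumeration, chi-square without continuity correction | 85.4% | 56.6% |

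At the cited rates the unpooled approximation gives 53.3% and the arcsine 62.7%. None reaches 80%.

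**Step 4: size of the gap.** The assumed rates are 10/5.3 = 1.9 and 1/0.5 = 2.0 times the cited ones. The assumed difference is 9.0/4.8 = 1.9 times the cited difference. With control at 0.5% and 100 per arm, the intervention rate would have to be about 8.8% for 80% power.

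**The case against.** The best defence is that the article says the rates were set in accordance with reference 22, not that they equal its rates. The Background summarises that trial as a tenfold increase, and 10% vs 1% is tenfold. Monitoring also differs: two 2-week patches there, 30-second weekday recordings over 6 months before the comparison here. The cited trial required hypertension and this one does not. Observed rates need not carry over in either direction.

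Part of this stands. The figure of 53–57% is the power if the rates of reference 22 apply. A reader might infer that it is the trial's actual power, but the documents do not establish the true rates in this population. The rest does not rescue the wording. The sentence refers to detection rates, and sample size depends on absolute rates: nearly the same ratio at the cited level almost doubles the number needed (191 vs 100 per arm). The article does not offer longer monitoring as a reason.

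Three further inferences go beyond the documents:

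- **That power is only about 32%.** This is the figure for Fisher's exact test or a continuity-corrected chi-square. The Analysis section names the chi-square test for new AF, mentions no correction, and offers Fisher only for other outcomes.
- **That the plan ignores losses it expects.** The article says only "There is a potential for loss to follow-up in older patients who are frail". It gives no rate, describes contact after 3 days without a recording, and analyses by intention to treat. A participant who stops recording therefore need not leave the denominator.
- **That the sample-size arithmetic is wrong.** Step 1 shows that it is right for its inputs.

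**Conclusion.** The point holds as an unsupported design input. The protocol attributes 10% vs 1% to a study that it reports elsewhere as 5.3% vs 0.5%, and it gives no reason for roughly doubling both rates. The statement of 80% power is true for 10% vs 1%. At the cited rates, 200 participants give 52.5% by the formula that reproduces the plan's own number and 56.6% by exact enumeration of the chi-square test, and about 382 would be needed for 80%.

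These figures assume 100 analysed per arm, two-sided α of .05, no continuity correction, and the rates of reference 22 as the Background gives them. The result does not show that 10% is unattainable in this trial, nor that 200 participants are too few for every plausible effect.

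**What to change.** Keep the total at 200 and change the Sample Size section as follows:

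1. Remove or correct the attribution to reference 22. Either describe 10% vs 1% as an assumption about twice the rates of that study, or state the actual rationale for it.
2. State power as 80% for 10% vs 1%, and about 53–57% for the 5.3% vs 0.5% of reference 22.
3. If power under losses is also shown, label the loss rate as an illustrative assumption, since the article gives none.

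In the Analysis section, add that the risk difference in AF detection will be reported with its 95% CI alongside the chi-square test, and that a non-significant test will not be taken as absence of benefit. The chi-square test stays as planned.

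The cost is a few sentences and a less favourable power statement. No participants, data or procedures are added, so the change remains practicable although 112 people had been enrolled by December 2021 (Results section).
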